### Sample size calculation and statistical analysis

Our working hypothesis is that ultrasound-guided CA- versus IA-SB yield similar block dynamics. Thus, this study will be designed as a non-inferiority trial. In the previous studies using single or multiple injections in SB, we have observed that the proportion of patients with complete sensory blockade reached a plateau starting at 20 min after injection. It fluctuates between 70% and close to 100% within 30 min [3–6, 16]. In other words, relative to itself, the variation is very subtle from 20 to 30 min. The primary outcome is considered as the proportion of patients with complete sensory blockade of all 4 terminal nerves at 20 min after injection in this study. Based on a pilot study with 15 patients in each group, the proportion of patients with complete sensory blockade achieved was 73% in the CA-SB group and 87% in the IA-SB group (unpublished data). Therefore, we assume that a difference in proportion between the two groups less than − 5%, measured at 20 min after injection, will be considered non-inferiority. The required sample size per group is calculated to be 55 with a statistical power of 80% and a one-sided 95% confidence interval. To account for a possible 10% dropout rate, the total sample size is inflated to 122 participants (*n* = 61, per group).

Statistical analysis will be performed using *SPSS for Windows 18.0* (SPSS Inc., Chicago, IL). For continuous data, normality will be first assessed with the *Kolmogorov-Smirnov test* and then analyzed using an *independent-samples t test.* Categorical variables will be summarized as a frequency, *n* (%), such as the proportion of complete sensory or motor blockade, success rates, and adverse events, etc. The *Pearson χ*^*2*^
*test*, *Fisher’s exact test*, or a *Mann-Whitney U test* will be used for categorical variables as appropriate. A *p < 0.05* will be considered statistically significant for all results.

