**Methods:**

The total 122 patients undergoing elective upper extremity surgery will be randomly allocated to receive either an IA-SB or a CA-SB using a double-injection (DI) technique. In the IA-SB group, a portion of LA (15 mL) is injected accurately to the intertruncal plane between the middle and lower trunks under real-time ultrasound guidance; then, the remaining volume (10 mL) is carefully distributed to the other intertruncal plane between the upper and middle trunks. In the CA-SB group, the DI technique will be carried out as described in Tran’s study. The primary outcome is the percentage of patients with a complete sensory blockade at 20 min with a predefined non-inferiority margin of − 5%. The secondary outcomes include the sensory-motor blockade of all 4 terminal nerves, onset times of the individual nerves within 30 min, block-related variables, and adverse events.

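### The non-inferiority rule is written backwards and without a confidence limit: a difference below −5% is called non-inferior, so a clearly worse IA-SB result would meet it

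*Protocol article*

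**What the plan says.** The criterion stands in the protocol article under Sample size calculation and statistical analysis. After the pilot rates, the text says "we assume that a difference in proportion between the two groups less than" −5%, "measured at 20 min after injection, will be considered non-inferiority". The groups are not put in order, and no confidence limit is mentioned.

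The next sentence gives the sample size: "The required sample size per group is calculated to be 55", with "a statistical power of 80% and a one-sided 95% confidence interval". This is the only place where the interval appears, and there it is a planning input.

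The Methods part of the abstract gives the margin alone, "with a predefined non-inferiority margin of" −5%, without a rule for applying it. The analysis paragraph lists Pearson chi-square, Fisher's exact and Mann-Whitney tests for categorical variables, with p < 0.05 for all results. It compares no interval with the margin.

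**The concern.** The sentence has three defects.

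- **Direction.** More patients with complete blockade is better, so a negative margin belongs to the difference IA-SB minus CA-SB. Observed differences of −6 or −15 points are less than −5 and lie on the inferior side. The sentence calls them non-inferior.
- **Order of subtraction.** It is not stated, and neither order rescues the sentence. Under CA-SB minus IA-SB, a value below −5% would require IA-SB to be more than 5 points better, which is not a non-inferiority rule.
- **Estimate or limit.** The threshold is applied to the difference measured at 20 min, not to a confidence limit. A reader who corrects only the sign is left with a rule that ignores sampling error.

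The primary conclusion depends on this sentence. As it stands, several readings can be chosen after the data are seen. An observed difference of about −4 points would pass under one and fail under another.

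**Working it through.** **Inputs.** All come from the sample size section: pilot rates ("was 73% in the CA-SB group and 87% in the IA-SB group"), margin −5 points (also in the abstract), one-sided 5% level, power 80%, 55 per group. Below, d is the IA-SB proportion minus the CA-SB proportion.

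**Step 1: reproduce the planned sample size, to see which rule it was built for.** For a test of d against −0.05, with z(0.95) = 1.645 and z(0.80) = 0.842, so that the squared sum is 6.183:

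- Separate variances: n = [0.73 × 0.27 + 0.87 × 0.13] × 6.183 / (0.14 + 0.05)² = 0.3102 × 6.183 / 0.0361 = 53.1, rounded up to 54.
- Pooled variance, mean proportion 0.80: n = 2 × 0.80 × 0.20 × 6.183 / 0.0361 = 54.8, rounded up to 55. This is the stated figure.
- One-sided 2.5%, separate variances: 68. This does not match.
- Requiring IA-SB to be more than 5 points better (the literal sentence under CA-SB minus IA-SB): n = 0.3102 × 6.183 / (0.14 − 0.05)² = 236.8, rounded up to 237. This does not match.

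So the 55 per group belongs to a one-sided 5% test of IA-SB minus CA-SB against −5%.

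**Step 2: compare three rules by exact binomial enumeration**, with 55 per group and CA-SB at 73%. The lower limit is d − 1.645 × √[p_IA(1 − p_IA)/55 + p_CA(1 − p_CA)/55], using observed proportions. Entries are the probability of declaring non-inferiority.

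| True IA-SB rate | True difference | Literal: d < −5% | Sign reversed: d > −5% | Lower limit > −5% |
|---|---|---|---|---|
| 53% | −20 points | 0.956 | 0.044 | 0.001 |
| 58% | −15 points | 0.878 | 0.122 | 0.003 |
| 63% | −10 points | 0.732 | 0.268 | 0.014 |
| 68% | −5 points (at the margin) | 0.521 | 0.479 | 0.053 |
| 73% | 0 | 0.295 | 0.705 | 0.153 |
| 87% | +14 points (pilot) | 0.007 | 0.993 | 0.817 |

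With a Newcombe interval instead of the Wald interval, the error at the margin is 0.049. At 61 per group, the sign-reversed rule errs at the margin with probability 0.535.

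**Step 3: three example results**, each with CA-SB at 40/55.

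| IA-SB | d | Lower limit | Literal rule | Sign-reversed rule | Confidence-limit rule |
|---|---|---|---|---|---|
| 30/55 | −18.2 points | −33.0 | met | not met | not met |
| 38/55 | −3.6 points | −17.9 | not met | met | not met |
| 48/55 | +14.5 points | +2.2 | not met | met | met |

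The literal rule accepts the worst of the three results and rejects the best.

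**The case against.** The strongest reply is that nobody would apply the sentence literally. The article describes a non-inferiority design, states a hypothesis of similar block dynamics, and gives a negative margin on a favourable outcome. Its own pilot result would fail the literal rule. The wording is most likely a slip for a deficit of less than 5%, and the sample size was computed for the proper rule. On this view, 0.88 and 0.007 describe a rule that will never be used.

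The sentence also never says observed difference. It can be read as stating a margin for the true difference, with the one-sided interval following directly. The 0.48 then arises only for a reader who sets that interval aside. Finally, the full protocol or an analysis plan, neither shown here, may spell out the comparison with the limit.

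Much of this stands. The intended rule can be recovered, and the missing confidence limit is the softer half of the point. It does not make the written rule right. The reversed inequality is stated text, not something left to another document, and an analysis plan with the proper rule would contradict the published article. A prespecified criterion should not have to be worked out backwards from a sample size.

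**Conclusion.** The point holds: the rule is wrong as written, in either order of subtraction, and it governs the primary conclusion. The sample size is not affected. With 55 per group and the pilot rates, the confidence-limit rule has power of about 82% and an error at the margin of about 5%, as planned.

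The size depends on the reading. Taken literally as IA-SB minus CA-SB, the rule is met with probability 0.88 when IA-SB is 15 points worse and 0.007 at the assumed rates. With the sign reversed but the observed difference still judged, the false claim rate at the margin is 0.48, roughly ten times the planned 0.05. These figures assume independent binomial outcomes, CA-SB at 73% and 55 analysed patients per group. They describe what each reading would do, and are not a forecast of how the trial team will analyse the data.

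**What to change.** Replace the sentence with: *The difference is the IA-SB proportion minus the CA-SB proportion at 20 min. Non-inferiority is concluded only if the lower limit of the one-sided 95% confidence interval for this difference is greater than −5 percentage points.* Name the same interval in the analysis paragraph as the primary analysis, so that the chi-square and Fisher tests with p < 0.05 are not taken for the non-inferiority test.

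The cost is a sentence of text. The margin, the 55 per group, the total of 122 and the conduct of the trial stay as they are. The correction should be dated and made before the primary outcome is compared between groups. If that comparison has already been made, the report should say so and state the rule that was applied.

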**Other secondary outcomes**		
Imaging time	Defined as the time from initial contact of the ultrasound probe with the skin until obtaining satisfactory imaging.	A stopwatch to calculate
Needle time	Defined as the time from initial needle insertion until the complete injection of the LA.	A stopwatch to calculate
Performance time	Defined as the imaging time plus the needle time.	/
Satisfactory imaging	Defined as more than 4 divisions of the plexus should be visualized as hypoechoic circular structures lateral to the subclavian artery for the CA-SB, and all 3 trunks of the plexus (upper, middle, and lower) for IA-SB.	Real-time ultrasonic image
Needle pass	Defined as at least 10-mm withdrawal of the needle to retract its trajectory.	During puncture
Needle visual score	Converted into a 5-point scale^§^	Assessment will be made at the time when the first proper position for LA injection is confirmed.
Procedural-related pain	Converted into the numeric rating scale (NRS)	NRS: 0 = no pain, 10 = worst possible pain
Difficult level	Converted into the NRS	NRS: 0 = no difficulty, 10 = extremely difficulty
Surgical anesthesia	Defined as one can tolerate surgical stimulus	During skin incision
The percentages of patients with a complete sensory or motor blockade	The combined score is equal to or greater than 7 points.	The percentages of patients with complete sensory or motor blockade using a validated 3-point scale^#^ every 5 min until 30 min after injection.
Sensory onset time	The time point when combined score is equal to or greater than 7 points.	Using a validated 3-point scale every 5 min until 30 min after injection.
Motor onset time	The time point when combined score is equal to or greater than 7 points.	Using a validated 3-point scale every 5 min until 30 min after injection.
Sensory-motor onset time	The time point when the combined score is equal to or greater than 14 points.	Using a validated 3-point scale for complete sensory-motor blockade every 5 min until 30 min after injection.
Duration of the sensory-motor blockade	Converted into the NRS	0 = normal compare that to the contralateral upper limb, 10 = no feeling or complete in-mobility; sensory-motor blockade return to normal will be defined as NRS<3.

*3-point scale for sensory blockade: 0 = no block, 1 = partial anesthesia, 2 = complete anesthesia

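### Onset times are right-censored at 30 min, but the only method named for continuous data is a t test, which has no place for patients who never reach the threshold

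*Protocol article*

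**What the plan says.** The abstract counts "onset times of the individual nerves within 30 min" among the secondary outcomes. Table 1, under other secondary outcomes, defines sensory onset and motor onset in the same words, "The time point when combined score is equal to or greater than 7 points", and sensory-motor onset as "The time point when the combined score is equal to or greater than 14 points". All three are scored every 5 min and scoring ends at 30 min.

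The statistics section gives one path for continuous data: "For continuous data, normality will be first assessed with the" Kolmogorov-Smirnov test, "and then analyzed using an *independent-samples t test". It names no alternative if normality fails. The Mann-Whitney test appears only in the list that "will be used for categorical variables as appropriate". No value, rank or censoring rule is given for a patient who does not reach the threshold.

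On how many patients reach complete sensory block, the sample-size paragraph says of earlier studies: "It fluctuates between 70% and close to 100% within 30 min". It describes a plateau from 20 min and gives pilot rates at 20 min of 73% (classical) and 87% (intertruncal), from 15 patients per group.

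Table 1 also lists, as a separate secondary outcome, the percentages with complete sensory or motor block, assessed "using a validated 3-point scale^#^ every 5 min until 30 min after injection".

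**The concern.** An onset time that cannot be seen beyond 30 min is a right-censored time on a grid of six values (5, 10, 15, 20, 25, 30). A t test needs a number for every patient. Those who fail to reach the threshold have none, so they either leave the comparison or receive a number that the plan does not define.

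If they leave, the comparison is no longer between randomised groups. It is between those in each arm whose block succeeded, and the two arms may lose different shares. An arm with more failures can then look as fast as the better arm. An arm that converts slow patients into late successes can look slower because of those successes.

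This matters because the Background section counts onset times as part of block dynamics, and comparable block dynamics is the trial's hypothesis. A reader will take a table of mean onset times as evidence on that question.

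**Working it through.** **Inputs from the protocol.** Onset definitions, 5-min grid and 30-min limit (Table 1). Pilot rates of 73% and 87% at 20 min, the 70% to near 100% range, and 55 per group (sample-size paragraph). The plan gives no planning figure for onset. Its 55 per group, used below as the arm size, does reproduce. With pooled rate (0.73 + 0.87)/2 = 0.80, the formula gives 2 × 0.80 × 0.20 × (1.645 + 0.842)² / (0.14 + 0.05)² = 54.8, so 55.

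**How many patients have no sensory onset time.** If the 20-min pilot rates held unchanged to 30 min:

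- classical: 0.27 × 55 = 14.9, about 15 patients
- intertruncal: 0.13 × 55 = 7.2, about 7 patients

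Over the protocol's own range the number runs from about 0 to 0.30 × 55 = 16.5 per arm. The protocol gives no rates for motor or sensory-motor onset.

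**Scenario A, pilot-like.** Only the 20-min points come from the protocol; the rest is assumed. Cumulative share reaching the threshold:

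| Minutes | 5 | 10 | 15 | 20 | 25 | 30 |
|---|---|---|---|---|---|---|
| Classical | 0.05 | 0.25 | 0.52 | 0.73 | 0.76 | 0.78 |
| Intertruncal | 0.05 | 0.28 | 0.60 | 0.87 | 0.90 | 0.92 |

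Let S be the sum of each grid time multiplied by the increment in the curve at that time.

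- Classical: S = 5(0.05) + 10(0.20) + 15(0.27) + 20(0.21) + 25(0.03) + 30(0.02) = 11.85
- Intertruncal: S = 5(0.05) + 10(0.23) + 15(0.32) + 20(0.27) + 25(0.03) + 30(0.02) = 14.10

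Mean among reachers is S divided by the share reaching by 30 min:

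- 11.85/0.78 = 15.19 min (classical)
- 14.10/0.92 = 15.33 min (intertruncal)

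The mean restricted to 30 min, over all patients, is S + 30 × (share not reaching):

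- 11.85 + 30 × 0.22 = 18.45 min (classical)
- 14.10 + 30 × 0.08 = 16.50 min (intertruncal)

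The near-2-minute advantage over all patients (18.45 − 16.50 = 1.95) disappears among reachers. In simulated trials with 55 per arm and two-sided 5% tests, the t test on reachers rejects about 5% of the time, its false-positive level. A log-rank test with censoring at 30 min rejects about 37%.

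**Scenario B, extra late reachers.** Assumed curves: classical 0.10, 0.35, 0.60, 0.73, 0.73, 0.73; intertruncal 0.10, 0.35, 0.60, 0.80, 0.90, 0.95. The intertruncal arm is equal or better at every check.

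- Classical: S = 0.5 + 2.5 + 3.75 + 2.6 = 9.35; mean among reachers 9.35/0.73 = 12.8 min
- Intertruncal: S = 0.5 + 2.5 + 3.75 + 4.0 + 2.5 + 1.5 = 14.75; mean among reachers 14.75/0.95 = 15.5 min

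The arm that blocks more patients appears 2.7 min slower, and the t test rejects in 59% of simulated trials. The restricted means order the arms correctly: 9.35 + 30 × 0.27 = 17.45 against 14.75 + 30 × 0.05 = 16.25 min.

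**Giving non-reachers a number.** Entering 30 min for each of them reproduces the restricted mean. That is a sound summary if declared as such, but reported as mean onset it equates failure with success at 30 min. Any later value shifts the result by choice. The plan declares neither.

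**The case against.** The statistics section never mentions onset time alongside the t test and never says that non-reachers are left out. A reader might infer that the protocol expressly does both; it does not. Onset on six grid points could be treated as ordinal and given to the Mann-Whitney test, with failures ranked last. How to score patients without an event is also a detail that an analysis plan often settles. This part stands as a limit on the wording. It does not remove the point: onset is a measured time, the t test is the only method named for continuous data, and Mann-Whitney is tied to categorical variables. The difficulty is that the named method does not fit the outcome, beyond any missing detail.

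A second objection is that the difference lost from the onset comparison is visible elsewhere. This stands. The complete-block percentages at each 5-min check include failures, and the statistics section assigns chi-square or Fisher tests to such proportions. In Scenario A, a chi-square test of the 30-min percentages rejects in about 54% of simulated trials, more often than the log-rank test. So a reader who inferred that the plan would hide a real difference from the trial as a whole would be going too far.

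A third objection concerns size. With 95% against 76% reaching by 30 min and the same onset pattern among reachers, the log-rank test rejects about 69% of the time against 5% for the t test. That rests on an assumed 19-point gap, larger than the pilot's 14 points at 20 min, and should not be read as the expected effect here.

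**Conclusion.** The concern holds for the three onset outcomes and no further. They are right-censored at 30 min, a non-trivial and possibly unequal share of patients may have no value, and the only continuous-data method named cannot use those patients. Under pilot-like curves, a restricted-mean difference of about 2 min over all patients becomes 0.1 min in the other direction among reachers, with about 5% rejection for the t test against about 37% for the log-rank test. Under a late-reacher pattern, the arm that blocks more patients can look slower.

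These sizes depend on assumed curves. Only the 73% and 87% points and the 70% to near 100% range come from the protocol, and the pilot had 15 patients per group. They also assume that onset follows the continuous-data route and that non-reachers are excluded, which the text implies but does not state. The binary primary outcome, the sample size and the 5-min block percentages are unaffected. Onset is listed among the other secondary outcomes, so this should be corrected but does not threaten the main conclusion.

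**What to change.** State that sensory, motor and sensory-motor onset will be analysed in all randomised patients, with those not reaching the threshold censored at 30 min. Report the cumulative incidence at each 5-min check, compare arms with a log-rank or discrete-time (complementary log-log) test suited to grouped times, and give the restricted mean time to 30 min with its difference between arms. A rank test with non-reachers placed last would also be acceptable if named in advance. Keep the t test for continuous measures observed in full, such as imaging time and needle time.

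The cost is a few sentences of analysis wording and slightly more analysis work in standard software. No new data, visits or patients are needed, since the 5-min scores are already collected.

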**Most important secondary outcomes**		
Nerve injury	The percentages of patients who have been associated with persistent paresthesia or weak of the operative upper limb.	7 days after surgery via post-operation follow-up at the ward or telephone follow-up.
Incidence of adverse events	The percentages of patients who have been occurred with vascular puncture, Horner syndrome, toxicity of LA, or pneumothorax.	According to drawing with blood, real-time ultrasonic image, and (or) the patient’s symptoms. A detailed description is seen in the footnote^£^.
Diaphragmatic paralysis	The excursion of the ipsilateral hemidiaphragm will be measured by ultrasound in supine position via the anterior subcostal route in centimeters.	Using ultrasonic evaluation at 35 min after injection.

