In the previous technique-related trials, the more needle passes seem the shorter onset time and better sensory-motor blockade [7]. However, the shorter onset time associated with the incremental needle passes is counterbalanced by its longer performance time and is accompanied with a high risk of intraneural injection [3–6, 16]. Nonetheless, the most used and teaching needling technique is the DI technique because, with an acquired satisfactory learning curve, the trainees can implement relatively safe skills while retaining the benefit of quick onset [26, 27]. In addition, we also observed that, in many patients, rather than being a singular entity, the neural cluster is composed of more than one main satellite clusters after the first injection [6, 8]. Finding a better approach for better LA diffusion based on the advancement in ultrasound guidance might be a meaningful technological innovation. Excitingly, the novel IA is just performed between the epineurium of the 3 trunks, and it aims to anesthetize the brachial plexus where the 3 trunks can be visualized as independent of hypoechoic nodules [12]. The authors have proposed that this approach can provide complete blockade of all 4 terminal nerves and satisfying onset times while avoiding intraneural injection and pleural puncture. In our study, the sensory-motor blockade-related clinical parameters including the percentage of patients with complete blockade at all the predetermined intervals, onset times, and adverse events will be recorded. As the IA is closer to the interscalene, an important issue concerning the potential risks of diaphragmatic paralysis is another important dimension of safety [28, 29]. The excursion of the ipsilateral hemidiaphragm will be measured by M-mode ultrasonography in supine position via the anterior subcostal route in centimeters at 35 min after injection [30]. We will also observe the duration of sensorimotor block and potential nerve injury after surgery. The results can help us to determine the efficacy and safety of an IA with the DI technique.

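### One unadjusted p < 0.05 rule covers all 17 secondary outcomes, so secondary findings lack the 5% error rate it implies; the primary non-inferiority test is unaffected

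*Protocol article*

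**What the plan says.** The protocol article names one primary contrast under 'Sample size calculation and statistical analysis': "The primary outcome is considered as the proportion of patients with complete sensory blockade of all 4 terminal nerves at 20 min after injection". The Abstract gives it a "predefined non-inferiority margin of" −5%, and the trial is sized "with a statistical power of 80% and a one-sided 95% confidence interval".

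The same section closes with one threshold for everything: p < 0.05 "will be considered statistically significant for all results". It gives no testing order, no division of alpha, and no statement that the secondary outcomes are exploratory.

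Table 1 sorts the secondary outcomes into two tiers. The upper tier, "Most important secondary outcomes", has three rows: nerve injury, adverse events and diaphragmatic paralysis. The lower tier has 14 rows. One of these is "The percentages of patients with complete sensory or motor blockade using a validated 3-point scale", assessed every 5 min to 30 min. The tiers share the same threshold.

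The Discussion says of the outcomes it reviews: "The results can help us to determine the efficacy and safety of an IA with the DI technique".

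**The concern.** This is not just a detail left to an unseen analysis plan. The article states a rule and applies it to every result, so a later plan that treated the secondary outcomes as exploratory would have to depart from that sentence.

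Followed as written, an isolated p < 0.05 for motor block at 10 min, needle time or an onset time would be reported as a significant difference, with the same standing as any other result. The error can favour either approach. It matters here because the working hypothesis is about similar block dynamics. The Background describes these as including complete sensory-motor blockade and onset times, and most of those measures are secondary.

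The rule also misleads in the other direction for safety. A result above 0.05 on a rare event could be read as showing no harm.

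**Working it through.** **The plan's own figure.** The article states no familywise error rate. The figure it does give in this section is the primary sample size. The inputs are "73% in the CA-SB group and 87% in the IA-SB group", margin 5 points, one-sided 5% and power 80%. With mean rate 0.80 and distance to the margin 0.14 + 0.05 = 0.19, n = 2 × 0.80 × 0.20 × (1.645 + 0.842)² / 0.19² = 54.8, so 55 per group as stated. The sizing rests on one comparison only.

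**Counting the secondary comparisons (Table 1).**
- Blockade row: 6 times × 2 modalities = 12, less the primary (sensory, 20 min) = 11.
- The other 16 rows at one comparison each: 16.
- All 17 rows: 16 + 11 = 27, or 30 if the four adverse events are tested separately.
- Working figure: 27 − 3 = 24, leaving out nerve injury, adverse events and satisfactory imaging. These are likely to be sparse or near-constant, and Fisher's test is then conservative.
- Counting only the 14 rows of the lower tier also gives 24 (13 + 11), but that is a slightly different set. The total is therefore about 24, not exactly 24.
- The Abstract also names onset times of individual nerves, which are not counted here.

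**Chance of at least one p < 0.05 if no secondary outcome truly differs.** Under independence this is 1 − 0.95^m:

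| m | Chance | Expected number (0.05 × m) |
|---|---|---|
| 17 (one test per row) | 58% | 0.85 |
| 24 | 71% | 1.2 |
| 27 | 75% | 1.35 |
| 30 | 79% | 1.5 |

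**Allowing for correlation.** The documents give no correlations, so these are assumed. Simulation of 24 equally correlated two-sided tests at 0.05 gives:

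| Correlation | 0.2 | 0.3 | 0.5 | 0.7 | 0.8 | 0.9 |
|---|---|---|---|---|---|---|
| Chance | 65% | 59% | 46% | 31% | 24% | 16% |

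With one test per row (m = 17), correlation 0.5 gives 38% and 0.7 gives 27%. The 11 blockade comparisons alone give 38%, 32% and 20% at serial correlations of 0.5, 0.7 and 0.9.

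**Patient-level check.** A null simulation used the 24 lower-tier comparisons with 61 patients per arm. It assumed a latent sensory-motor correlation of 0.7, read onset from the 5-min grid, built performance time as imaging plus needle time, and used Fisher's test for sparse tables. It gave about 50%, with about 1.0 false positive expected. That count is below 1.2 because tests on sparse tables do not use their full 5%.

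**Safety direction.** If no event is seen in 61 patients, the one-sided 95% upper limit is 1 − 0.05^(1/61) = 4.8%. A non-significant comparison would not rule out a rate of that size.

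**The case against.** Several objections carry weight.

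- **The confirmatory claim is untouched.** There is one primary outcome, at one time, with one margin, and nothing makes trial success depend on a secondary outcome. Unadjusted tests of prespecified secondary outcomes are also common. This stands, and it keeps the severity low to moderate.
- **A test at every time point is inferred.** Table 1 says blockade is assessed every 5 min. The statistical section says such proportions will be summarized as frequencies, with tests used as appropriate. This stands, which is why 24 is conditional. With one test per row the chance is still 27% to 38% at correlations of 0.7 to 0.5.
- **Independence is unrealistic.** Performance time is the sum of two other outcomes. The 11 blockade comparisons and three onset times, 14 of the 24, are read from the same sensory and motor scores. This stands. A reader might infer from 71%, about 14 times the nominal 5%, that a false finding is more likely than not; Table 1's own definitions rule out the independence that figure needs.
- **The global null may be false.** The approaches differ in needle targets and imaging requirements, so some procedural outcomes may truly differ. The figures describe only outcomes with no true difference.
- **The Discussion can be overread.** A reader might infer that the efficacy and safety conclusions rest on secondary results. The sentence says only that the results can help, and the outcomes it covers include the 20-min primary.

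What does not stand is that this is only an omission from a condensed article. The sentence sets a threshold for all results. It is true that it declares no particular outcome significant.

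**Conclusion.** The point holds as a minor to moderate wording defect. Applying an unadjusted 5% threshold to all secondary outcomes gives the set of secondary findings an error rate well above 5%. A chance of roughly 25% to 50% of at least one false nominal finding is a fair range, or about 5 to 10 times the nominal level, with about 1.2 expected if every test uses its full 5%.

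The range assumes about 24 two-sided tests, no true secondary difference, and average correlation from about 0.5 to 0.8. The patient-level check supplies the upper end. Weaker correlation would raise the figure towards 71%, and correlation near 0.9 would lower it to about 16%.

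The documents do not support the stronger reading that the trial's main conclusion is compromised. The 20-min non-inferiority comparison has its own criterion, and its error rate does not change with the number of secondary tests.

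**What to change.** Replace the closing sentence of 'Sample size calculation and statistical analysis' with text to this effect:

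> The only confirmatory test is non-inferiority of IA-SB to CA-SB for complete sensory blockade at 20 min. All secondary outcomes, including blockade at the other time points, are exploratory or supportive and are reported as between-group differences with 95% confidence intervals. Any p-values for them are nominal and unadjusted. Safety outcomes are reported descriptively with confidence intervals, and a non-significant difference is not taken as evidence of no harm.

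If a confirmatory claim is wanted on an outcome in the upper tier of Table 1, such as hemidiaphragm excursion, test it only after the primary succeeds and in a pre-stated order.

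This needs no extra patients or data and no change in sample size. The loss is that an isolated nominal p < 0.05 on a secondary outcome can no longer be presented as a confirmed difference. The change is best made before unblinding. The planned study period ended on 31 August 2021, before publication on 29 January 2022, and the article does not say whether the data have been unblinded. If that point has passed, the results report should apply the same labelling.
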